A flow chart for 2YL is presented in Figure 2. Twelve PHUs have been identified by local partners, and matched into pairs with corresponding delivery rates and distance to a referral hospital (Appendix 1). From these pairs, PHUs will be randomly allocated into intervention sites and control sites. With established approval from the Ministry of Health and Sanitation, health leaders at a district level will be approached by local research staff with an invitation for their PHUs to participate in the study. On the basis of local baseline data, we estimate that 36 women per PHU will participate, approximately 216 women per arm (Figure 1) (details of sample size calculations in page 23). In the event of changes to the PHUs serving a community during the study period (e.g. existing PHUs closing, new PHUs opening), we may invite a PHU to participate in the same randomised arm if it is serving the same community . Our rational is that this is a trial of a community-based intervention, we have allocated a treatment arm to the community, and the community are now accessing another facility. This approach will help us to maintain recruitment to both arms. For example, Yataya community has been randomised to the control arm. The new PHU that recently opened there will be automatically allocated to the control arm. We may also conduct a community based survey in those clusters with low numbers of pregnant adolescent girls to understand if numbers included in the trial are real or if there is overreporting of age in facilities.

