**Recruitment, consent, data collection** ≈**3-6 and** ≈**9-12 months**

Interviews, focus groups, photovoice

**(Routine data collection at 1year** (routine PHU visit)

**(Routine data collection at 1year** (routine PHU visit)

Figure 2. Two Young Lives pilot study flowchart

Randomisation

The unit of randomisation is the trial area (or cluster), rather than individual woman. The sixteen trial areas will be allocated cluster numbers. Randomisation will be managed via a secure web-based randomisation and data management system hosted by MedSciNet with telephone back-up available at all times. Randomisation to intervention sites (2YL) and control sites (usual care) will occur in a 1:1 ratio. A minimisation algorithm will be used to ensure balance between the groups with respect to PHU use and distance to referral hospital. MedSciNet will write the randomisation program and hold the allocation code.

Intervention: 2YL mentoring scheme + usual maternity care

Women in the intervention group will receive the 2YL mentoring scheme provided as an adjunct to usual maternity care. Using the TIDieR reporting guidance^11^, a description of the intervention is as follows:

*Brief name*. 2 Young Lives mentoring scheme for pregnant teenagers and young mothers in Sierra Leone.

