*What? (Procedures) and How? (Modes of delivery)*. Weekly meetings between mentor and mentee; going to a local health facility with mentee to register for antenatal care, and reminding to attend or attending with mentee for usual antenatal care; accompanying mentee to health facility when in labour or needing emergency care (or ensuring other birth partner is available according to mentee’s wishes); flexible support postnatally dependent on mentee’s support network; discussion with mentee to consider small business options and accompanying mentee to purchase first supply of goods; monthly site meetings with all mentors and mentees for social interaction, cooking, eating and group discussion using Welbodi health cards; visits from mentor to mentee’s family to advocate for family support, if safe and appropriate; a face-to-face training for teachers in each of the 8 intervention sites. Graduation celebration at the end of the mentoring scheme.

*Who provided?* Mentors and teachers are trained by an experienced educationalist with experience of training both cadres. Mentors are women selected from communities where mentoring will take place, recruited based on having a reputation for kindness and being trustworthy, and an existing interest in young women’s issues. Visitors at monthly meetings are HCPs from local health facilities, or other or other community members who talk about educational or training opportunities.

*Where?* Mentoring takes place in agreed venues in the community where the mentee feels comfortable and where mentee and mentor can have a confidential conversation. Monthly meetings take place in a location in the community where there is shaded space for a group of 15-20 to cook (outdoors on a fire) and eat; many villages have these shared spaces, or mentors’ compounds where there is tree-shade.

*When and how much?* Girls are recruited at any stage of pregnancy, and have at least weekly mentoring as described, until baby is one year old.

*Tailoring?* If mentees are identified who have physical or intellectual disabilities, the programme is tailored to their needs where possible. For example, by providing communication cards for a deaf girl to use in labour, or by monitoring a girl with a learning disability taking pregnancy medication.

*Modifications? 10. How well planned? 11. How well actual?* These elements will be reported on at points in the research cycle when formative evaluation of implementation is undertaken.

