# Outcome measures

**Primary feasibility outcomes**:

Eligibility, recruitment, retention and attrition rates

Randomisation, data collection and data completeness

Selection of most appropriate primary outcome measure and sample size calculation

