# Data analysis

# Sample size calculation

Sample size estimation has been provided by the trial statistician, [name], co-investigator and Reader in Medical Statistics, KCL. Based on experience with some of the proposed trial areas and global maternal health literature relevant to these settings^3,6^, we estimate the risk to adolescent pregnant women in Sierra Leone of experiencing a primary outcome (one of maternal death or stillbirth or neonatal death with no double counting) to be approximately 20% of all adolescent women. We also estimate a modest intra-cluster correlation of 0.02 (sites similar but not identical, and a simple exchangeable autocorrelation structure based on previous experience in Sierra Leone)^6^.

Prior to full proposal development, the 2YL team visited a typical peri-urban PHU similar in size and distance to referral hospital to trial sites. At least 16% of all deliveries among teens resulted in maternal death, stillbirth or early neonatal death. It was not possible to include late neonatal deaths up to 28 days. In addition, girls who were referred to a referral hospital in an emergency were not included in these numbers. We believe that this data can match the indicative estimate of 20% of girls experiencing a primary outcome.

This study is planned as a pilot, with main stated aim to demonstrate the feasibility of a fully powered study, and to help with its design. But for the purpose of the power calculation (intention to treat and not per protocol), an assumption of at least 42 deliveries per site has been made, with 20% having primary outcome composite events during the trial duration.  These numbers will provide 84% power to detect a 52% relative risk reduction (RRR) of the primary outcome (from 20% to 9%) assuming a models ICC 0.02.

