# Proposed analysis

We will undertake two statistical analyses: one pragmatic, intention to treat analysis (ITT) to compare intervention and control clusters that include all adolescent girls as originally allocated after randomization; and a complementary per protocol (PP) analysis to compare intervention and control clusters that includes only those girls who completed the intervention originally allocated. The CONSORT guidelines for reporting of parallel group RCTs recommend that both ITT and PP analyses should be reported for all planned outcomes to allow readers to interpret the effect of an intervention. It is not possible to blind clusters to interventions they receive, but outcome assessments will be blinded.

The main analysis will be pragmatic and by logistic regression adjusting the standard errors for clustering. This gives equal weight to each woman. A secondary analysis using random effects generalised least squares (GLS-RE) will also be attempted, although past experience is that the model might not converge to give any useable results. We will adjust for important baseline differences that might be related to outcomes (e.g. parity, gestation at first antenatal visits). As individual-specific data will be used there is a potential for missing data; but the main impact of missing data would be to invalidate the randomised comparison if there was unequal dropout between the two arms, leading to potential boas. Multiple regression, as described, would correct for any such bias.

Qualitative data from interviews with women and focus groups discussions with mentors, healthcare providers and stakeholders with be analysed using Braun and Clarke's six-phase approach to thematic analysis^18^. In brief, this includes familiarisation with the data, generation of initial codes, the searching for and review of themes, naming and offering explanations for each theme, and lastly producing a report. This practical analytic approach involves inductive coding practices which are both consultative and initially open^19^, and thus helpful to explore the perspectives of different research participants, highlighting similarities and differences, and generating unanticipated insights^18^.

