We will pilot the use of photovoice as a participatory research methodology using small group discussions of photographs with young women. Photovoice is a photographic technique developed by Wang and Burrithat^20^ that puts cameras into the community members’ hands to help them to record, reflect upon, critically dialogue and share knowledge about their perspectives and priorities to reach policy makers^20,21^. These are all central elements of empowerment, a concept that is intertwined with the photovoice approach from its original conceptual underpinnings to its implementation^22^. While photovoice aims to foster social change, it can also enhance community engagement, increase awareness of community resources, and improve collaboration with research partners to help reduce health inequalities^23,20^ Photovoice has previously been used in vulnerable communites in Sierra Leone^24^ and other settings^-25-28^ Thus, this approach offers a unique opportunity and gain understanding about the social and cultural factors that may facilitate potential scale up and sustainability of the 2YL mentoring scheme in young women, that other research methods such as surveys and interviews may not fully capture.

Feasibility of health economics

It would not be appopiate to conduct a full economic evaluation for a pilot study designed to estimate the parameters needed to design a future definitive trial - should not provide estimates of treatment effectiveness because the samples often have no or limited power to reliably detect between group differences. Thus, the focus of health economics in this pilot trial will be limited to developing or refining service use schedules and other measures of outcomes (i.e. piloting of a metric for risk-benefit assessment previously used in LMICs).

We will explore the resource use associated with the mentoring scheme and savings or other service use impacts (e.g. examining clinical records, based on clinical opinions) and will also estimate costs associated with the delivery of the scheme (components will include, e.g. recruitment and training of mentors, stipends, bursaries for girls, social gatherings). Cost consequences analyses will be used to present the results from this pilot study, as the costs and effects observed can also be used in value of information modelling to determine whether the cost of a definitive RCT is worthwhile.

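### The secondary analysis is a random-effects GLS model that the plan itself doubts, with no fallback, so the main model may lack a usable check at 12 clusters

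*Protocol*

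**What the plan says.** Under Proposed analysis, the protocol names two models for the clinical comparison. The main one is logistic regression with standard errors adjusted for clustering, which by its own account weights every woman equally. On the other it says: "A secondary analysis using random effects generalised least squares (GLS-RE) will also be attempted, although past experience is that the model might not converge", and the sentence goes on to doubt whether any usable result would come out. It does not say what will be done in that case. Adjustment is planned for baseline differences, with parity and gestation at first antenatal visit as examples.

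The pilot's purpose bears on this. The primary feasibility outcomes include "Selection of most appropriate primary outcome measure and sample size calculation", and the health-economics paragraph calls the study "a pilot study designed to estimate the parameters needed to design a future definitive trial". The Study aim says that the later trial is a cluster RCT. The ICC appears only as a planning assumption of 0.02, under Sample size calculation.

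The number of clusters is not stated consistently. The design sections say "Twelve PHUs have been identified by local partners", but Randomisation says "The sixteen trial areas will be allocated cluster numbers" and the intervention description has "a face-to-face training for teachers in each of the 8 intervention sites". I use 12, which agrees with the site list, the flow chart (six per arm) and Appendix 1.

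**The concern.** A secondary analysis is useful here because the main one is fragile. Cluster-robust standard errors are large-sample quantities in the number of clusters, and with six per arm they tend to be too small. The planned second analysis should be one that can be relied on at 12 clusters. Instead the protocol names a model that it warns may fail and puts nothing behind it.

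The wording also leaves open which model is meant. Random-effects GLS in its usual two-step form estimates the variance components by moments and solves once, so it has nothing to converge. The warning suits a random-effects logistic model. The two readings give different effect measures (a risk difference or an odds ratio), and only the second would be on the same scale as the main analysis.

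At stake are the check on the clinical comparison and, through the same cluster-level data, a clear statement of how uncertain the ICC is before it is used to size the definitive trial.

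**Working it through.** **Inputs.** From the protocol: 12 clusters, six per arm; 36 women per cluster ("we estimate that 36 women per PHU will participate, approximately 216 women per arm") or 42 ("an assumption of at least 42 deliveries per site has been made"); control risk 20%; ICC 0.02. Appendix 1 lists 28 to 65 under-19 births per site. Assumed: two-sided 5%, and a normal reference for the regression models, because the protocol states neither.

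**The plan's own figure.** The ICC is used numerically only in the 84% power for 20% v 9%. Design effect = 1 + (42 - 1) x 0.02 = 1.82. Effective n per arm = 6 x 42 / 1.82 = 138.5. Power is 74.1% (pooled normal) or 66.1% (t on 10 df), not 84%. Eight clusters per arm give 85.4%, and a one-sided 5% test with six per arm gives 83.3%. That mismatch is a separate matter. It matters here because the cluster count fixes the degrees of freedom.

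**Type I error.** Beta-binomial trials with no treatment effect, risk 20%, ICC 0.02, using equal cluster sizes and the Appendix 1 sizes:

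| Analysis | Reference | Type I error |
| --- | --- | --- |
| Logistic, cluster-robust SE | normal | about 9-10% |
| GLS-RE (closed form) | normal | 6.6-7.1% |
| t test on 12 cluster proportions | t, 10 df | 5.0% |

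The cluster-level statistic is t = (mean proportion in one arm - mean in the other) / sqrt(s² x 2/6), where s² is the pooled between-cluster variance on 12 - 2 = 10 df. The critical value is 2.228, not 1.96.

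**Where the GLS-RE excess comes from.** With equal cluster size m, GLS-RE gives the same difference in mean proportions. Its squared standard error is 2 x max(MSB, MSW) / (6m), against 2 x MSB / (6m) for the cluster-level test. It is therefore never smaller. The excess over 5% comes from using 1.96 with about 10 df of information: P(|t| > 1.96) on 10 df is 7.8%, and setting negative variance estimates to zero brings this down to about 7%.

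**Precision of an ICC from 12 clusters.** ANOVA estimator: ICC = (MSB - MSW) / (MSB + (m - 1) x MSW), within arms. With a true value of 0.02 and risks of 20% and 9%:

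- m = 42: SD 0.020, 95% range -0.010 to 0.069, at or below zero in 15% of trials.
- m = 36: SD 0.023, 95% range -0.013 to 0.074, at or below zero in 19%.

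With 20% in both arms the ranges are -0.010 to 0.065 and -0.012 to 0.069.

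**Consequence for sizing.** Take the protocol's own target (20% v 9%, 84% power, 42 per cluster). Without clustering, n per arm is 178. Multiply by 1 + 41 x ICC:

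- ICC 0: 178, or 5 clusters per arm.
- ICC 0.02: 178 x 1.82 = 324, or 8 clusters.
- ICC 0.069: 178 x 3.829 = 682, or 17 clusters.

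**Efficiency cost of equal cluster weights.** For cluster variances proportional to ICC + (1 - ICC)/m and the Appendix 1 sizes, the variance of the unweighted mean is about 2% above the optimum at ICC 0.02, and about 8% above at ICC 0.

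**The case against.** The strongest reply is that this is a secondary analysis in a feasibility pilot, that estimator details belong in an SAP that is not shown, and that the trial will hold individual data labelled by site, so nothing is lost. Much of that stands, and it rules out three stronger readings that a reader might infer.

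- *The plan expects the model to fail.* It says only that the model might not converge.
- *A linear model is wrong for estimating the ICC of a yes/no outcome.* It is not: its ICC is on the proportion scale, which is the scale used in the design effect.
- *The pilot could finish with no ICC to be had.* It could not: the ANOVA estimator is closed-form, an exchangeable logistic GEE converged in all of 1,000 simulated trials, and the ratio of robust to naive variances in the main model also implies a value. No passage makes GLS-RE the source of the ICC, and naming an estimator is ordinary SAP content.

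Nor does the width of the ICC range count against GLS-RE. It comes from having 12 clusters, and no choice of estimator changes it.

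On type I error, the GLS-RE excess is modest and depends on the normal reference. With equal cluster sizes and a t reference on 10 df it would not exceed 5%. It is also fair that a t test on raw proportions would drop the planned covariate adjustment, so a two-stage version is needed.

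What the reply does not answer is the protocol text itself. It commits to a model, attaches a caveat that suits a different model, and provides nothing if the result is unusable.

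**Conclusion.** The point holds as a badly fixed secondary analysis, not as a failure to obtain the ICC. A simple alternative always returns a result and holds 5.0% type I error at 12 clusters, against about 7% for GLS-RE and about 9-10% for the main cluster-robust model, both with a normal reference. The case for a dependable check therefore rests more on the weakness of the main model than on GLS-RE itself.

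The figures assume 20% risk, ICC 0.02, beta-binomial variation between clusters, two-sided 5%, and an unpaired comparison of 12 clusters. Sixteen clusters would give 14 df. The protocol also describes matched pairs, and a paired analysis of six pairs would have 5 df.

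The ICC remark is secondary: any estimate from this pilot will be imprecise, and sizing on the point estimate alone could move the definitive trial between about 5 and 17 clusters per arm at the protocol's own target.

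**What to change.** In Proposed analysis:

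1. Replace GLS-RE with a cluster-level summary analysis: one proportion per cluster, compared between arms by t on 10 df.
2. For the adjusted version, use two stages: fit the individual covariates (parity, gestation at first visit) without the arm term, form observed-minus-expected residuals per cluster, and compare those by the same t test.
3. State the reference distribution for the main model as well.
4. Report the ANOVA ICC for the composite with a 95% CI, and size the definitive trial over that interval.
5. If a random-effects model is kept, say whether it is linear or logistic, and make the cluster-level analysis the stated fallback.

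Reconcile the twelve and sixteen cluster counts, since the degrees of freedom follow from them.

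The cost is protocol or SAP wording and a short analysis, with no new data. The drawbacks are a small loss of efficiency with unequal clusters (about 2% in variance at ICC 0.02), the extra stage for covariates, an ICC interval that will look wide, and equal weight per cluster, not per woman. The last could give a different effect from the main analysis if risk varies with cluster size.

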# Background and rationale for study

Maternal mortality in Sierra Leone is one of the highest globally (1,360 deaths per 100,000 live births in 2015)^1^ with teenage pregnancy a leading cause of death for mothers; teenage mothers are 40-60% more likely to die during childbirth.^2^ However due to ineffective maternal death reporting, this could be significantly higher. A household survey conducted in 2015 indicated a maternal death rate of 1 in 10 for under-18-year-olds in Eastern Freetown. A following study examined the causes of this high incidence of maternal death in teenagers and highlighted intersecting health and socio-economic vulnerabilities.^3^ Among key findings were that pregnant teenagers are often neglected by their families, particularly when being cared for by a non-parental adult, often sleeping on bare ground without a mosquito net, and are fed once a day in exchange for heavy domestic duties such as water collection and laundering, in many cases with little protection from ongoing gender-based violence. This lack of adult care or support often leads to delays in care-seeking or complete lack of antenatal and delivery care, putting teenagers at high risk of death from undetected pre-eclampsia, untreated infections, anaemia, lack of birth preparation, and common obstetric risks.^3^ To achieve the Sustainable Development Goals target of reducing the maternal mortality rate to less than 70 per 100 000 live births by 2030, adolescent girls are a priority group. ^4-6^

These findings led to the development of 2 Young Lives (2YL), a locally-designed intervention that provides mentoring from pregnancy through to one-year post-birth for women aged under-18. This encourages mentees to take up antenatal care and hospital birth, re-establish family connections where this is safe and appropriate, promotes health-seeking behaviour, provides practical advice about childbirth, parenting and contraception, and supports mentees to return to education or start vocational training. The 2YL scheme was piloted in 2017/2018 in an urban suburb of the capital, Freetown, and expanded to new sites in 2018, 2019 and 2021.^7^

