# How the 2YL intervention may work

Overall, the aim of 2YL is that mentees and their babies survive birth and the postnatal period, and that these young women are empowered economically and socially to thrive. A theory of change diagram in Figure 1 in page 8 illustrates how and why the 2YL intervention may work in young women in Sierra Leone.

After community engagement with key community stakeholders, volunteer mentors are recruited and trained to support mentees across a number of domains. The 4-day manualised training programme uses discussion, role play and bespoke pictorial maternal health resources to learn and share important health messages. Key ingredients of the mentoring scheme include a weekly one to one meeting, promotion of health services uptake, monthly social gatherings for peer support and health discussions, advocacy and practical advice, support to start and run small businesses, and encouragement to return to education or start vocational training.

There are a number of mechanisms whereby being mentored could lead to improved health outcomes for mothers and their babies:

- Mentors ensure that girls access antenatal care, often paying for routine drugs when not available in the clinics, and directly observing the girls taking them. They ensure birth with a Skilled Birth Attendant, a proven life-saving intervention. In addition, the timeliness and quality of this care, and the quality of interaction with the girl in the health facility may be improved by the her being accompanied by a known and respected older woman in the community^9^; mentors are often allowed to be present for birth. Getting to know a health worker through monthly facilitated discussions and regular antenatal care could also increase girls’ confidence in the health service, increasing their likelihood of seeking care in labour or in an emergency. Similarly, having a trustworthy adult in their lives also allows mentees to ask advice of mentors and access care promptly.
- Girls are economically empowered through their small businesses, which could lead to a better diet in pregnancy, potentially addressing risk factors for maternal mortality such as malnutrition and anaemia. This economic empowerment could also allow girls to make independent decisions when to go to hospital as they could pay for their own transport^10^.

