| Girl attends ANC but does not give birth in the PHU (maternal death, stillbirth or neonatal death may be missed) | Most likely girl has moved to another area    Liaise with referral hospital to cross-check birth register. If not there;  Data collector to visit address in AN register. If not found;  Connection with midwife investigators from MDSR teams in intervention sites to detect any maternal deaths in community. |
| Girl does not attend ANC but comes to PHU in labour | N/A. |
| Girl attends ANC at PHU but is referred for antenatal complication (very young, very small, sickle cell, twins, breech etc) (maternal death, stillbirth or neonatal death in referral hospital may be missed) | Since she will not necessarily arrive by ambulance, she will be harder to track than emergency transfer in labour.  However, we will liaise with da or HCW at referral hospital to cross-check birth register. |
| Girl attends ANC at PHU but is transferred in labour as an emergency (maternal death, stillbirth or neonatal death in referral hospital may be missed) | Through regular liaison with the referral co-ordinator in nearest referral hospital will find outcome data on girls who are referred. |
| Girl gives birth at PHU but does not attend for 6-week PN appointment (neonatal death, postpartum maternal death might be missed) | CHWs are routinely sent out to check on women who default at 6 weeks. |

Data collection at intervention and control sites will be done by data collectors. Data collectors will be responsible for entering the data anonymised onto MedSciNet, the study-specific management system. To prevent double counting, the research assistant will use their regular visits to ensure no patient is counted twice according to patient identifiers (e.g., in the community and at facility or for maternal and neonatal death).

We are confident, (through interaction with local community workforce and current local initiatives to ensure maternal death reviews), that it is unlikely that most primary outcome events will be missed. We will apply a flexible approach to individualise our methodology according to local capacity and CHW workforce infrastructure.

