# Trial Management and oversight arrangements

Pre-pilot trial

From September 2021 (start of grant) to January 2022, we will employ a research assistant and a PhD student, conduct community engagement visits, create contacts at each trial site, secure ethical approval at each trial area institution, and confirm the data collection procedures.

Trial Registration

The trial will be registered with https://www.isrctn.com following ethical approval.

Trial duration

Randomisation will start in March 2022, community engagement, recruitment and training of mentors during April and May 2022 and intervention implementation will start in May/June 2022. Latest data collection will be June 2024.

Data Management

Source data will be kept in paper-based databases kept in secure areas of each facility and of the implementation partners Welbodi and Lifeline Nehemiah Project. Only healthcare providers, research assistants and trial coordinator will have access to these databases. All data entered on the MedSciNet database will be automatically stored and backed-up.

King’s College London holds responsibility for ensuring participants’ information is kept confidential. All paper documents will be stored securely and kept in confidence in compliance with the Data Protection Act (1998). Outcome data will be entered onto the electronic forms and undergo a number of validation checks to verify the validity and completeness of the data captured; the data will be automatically transferred for storage in the electronic anonymised database held by MedSciNet on behalf of the Sponsors. [name], KCL, is registered for use of personal data with Information Commissioner’s Office. The hosting company, MedSciNet has a ISO 27001 certificate. MedSciNet's solutions conform to relevant FDA, NIH, and HL7 standards, guidelines, and recommendations. The MedSciNet database will be maintained ‘live’ for at least one year following the end of the trial. A copy of the database is then kept on the KCL Server for an indefinite period and is the responsibility of the unit statistician, regulated by the Joint Clinical Trials Office. Backups of the MedSciNet central database are put into fire safe vaults for a minimum 10 years storage. If needed data can be transferred to DVD disks for even longer storage.

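### Gestation at first antenatal visit is listed as a baseline covariate, but it is mostly post-allocation and on the mentoring pathway, so adjusting for it would not estimate the intention-to-treat effect

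*Protocol*

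**What the plan says.** Under Proposed analysis, the protocol plans an intention-to-treat comparison of clusters that will "include all adolescent girls as originally allocated after randomization", by logistic regression with standard errors adjusted for clustering. It then states: "We will adjust for important baseline differences that might be related to outcomes (e.g. parity, gestation at first antenatal visits"). The same paragraph relies on this regression to correct bias from unequal dropout. It gives no rule for a girl who lacks a covariate value.

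Other sections bear on this covariate:
- Trial duration: "Randomisation will start in March 2022", with implementation from May/June 2022 and last data collection in June 2024.
- Intervention description (Procedures): mentoring includes "going to a local health facility with mentee to register for antenatal care".
- How the 2YL intervention may work: "Mentors ensure that girls access antenatal care".
- Intervention description (When and how much): "Girls are recruited at any stage of pregnancy".
- Data collection, scenario table: one expected case is "Girl does not attend ANC but comes to PHU in labour".
- Other secondary outcomes: the number of antenatal checks is an outcome, and being accompanied to register for ANC is a fidelity measure.

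**The concern.** A baseline covariate should be fixed before allocation, or at least be something the intervention cannot alter. Gestation at first antenatal visit meets neither condition for most girls here. Areas are allocated first, girls book later, and earlier or more complete booking is one of the ways the programme is meant to work. Conditioning on a mediator gives the effect that remains after the booking pathway is blocked. That is a different quantity from the intention-to-treat effect promised in the same section.

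The second difficulty is that the variable does not exist for a girl who first appears in labour. The protocol's own rationale links "delays in care-seeking or complete lack of antenatal and delivery care" to a high risk of death, so these girls are not a random subset. If mentoring works as intended, there will be fewer of them in the intervention arm.

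The pilot is meant to assess potential treatment effects and to inform the outcome and sample size of a full trial. An attenuated estimate carried forward could inflate that trial or make a useful programme look unpromising.

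**Working it through.** **1. Order of events.** Allocation starts in March 2022, mentors are recruited and trained in April and May, and mentoring starts in May/June. Data collection runs to June 2024. The first visits of girls pregnant during the trial therefore mostly follow allocation. The exceptions are girls who had already booked when their area was allocated.

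**2. Position on the pathway.** Mentors take girls to register, ANC access is a listed mechanism, and girls can join before booking. The protocol thus places the covariate between allocation and outcome.

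**3. Target effect.** The protocol gives no figure for this issue. The reference is its planning assumption of 20% v 9%:
- OR = (0.09/0.91) / (0.20/0.80) = 0.396; log OR = −0.927.
- Relative risk reduction (RRR) = 1 − 0.09/0.20 = 55%. The sample size section prints 52%, so I work from the two risks. The stated 84% power is not used.

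**4. Simple calculation.** Suppose a share s of the log OR acts through booking (assumption). The adjusted log OR is (1 − s) × (−0.927), applied to control odds of 0.25.
- s = 0.2: risk 10.6%, RRR 47%.
- s = 0.4: risk 12.5%, RRR 37%.
- s = 0.6: risk 14.7%, RRR 26%.

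**5. Booking scenarios.** Class girls as early, late or never ANC. Risk in class j is expit(a + b_j) in control and expit(a + b_j + d) in intervention. Solve a so that control risk is 20%, then d so that intervention risk is 9%; exp(d) is the adjusted OR. All shares and class odds ratios are assumptions, because the protocol gives none.

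| Scenario | Never ANC, control / mentored | Late ANC, control / mentored | OR late, never (v early) | Adjusted OR | Log OR removed |
|---|---|---|---|---|---|
| No difference | 0 / 0% | 50 / 50% | 2, – | 0.39 | none |
| Mild | 5 / 2% | 50 / 30% | 1.5, 3 | 0.44 | 12% |
| Moderate | 10 / 2% | 50 / 30% | 2, 4 | 0.51 | 27% |
| Strong | 20 / 5% | 50 / 25% | 2, 4 | 0.58 | 41% |
| Extreme | 20 / 2% | 50 / 20% | 3, 6 | 0.77 | 72% |

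The strong row in full:
- Control: 0.30 × 11.1% + 0.50 × 20.0% + 0.20 × 33.3% = 20%.
- Mentored: 0.70 × 6.7% + 0.25 × 12.6% + 0.05 × 22.4% = 9%.
- d = −0.548, so the adjusted OR is 0.58 and the share removed is 1 − 0.548/0.927 = 41%.

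**6. Losing never-attenders only.** If girls without a visit drop out and nothing else changes, control risk in the mild to extreme rows falls from 20% to 19.1%, 18.1%, 16.7% and 16.3%. The RRR among those left is 54%, 52%, 50% and 47%. These losses should not be added to those in step 5. The model assumes one conditional odds ratio across ANC classes, so its adjusted OR is the same with or without the never-attenders.

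**7. Carry-over to the full trial.** Required size is proportional to [p1(1 − p1) + p2(1 − p2)] / (p1 − p2)². With p1 = 20% and the unrounded risks from step 4, the ratio to the 20% v 9% design is about 1.5, 2.4 and 5.1 for s = 0.2, 0.4 and 0.6.

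**The case against.** Several points on the other side have weight.

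- **Effect on booking.** A reader might infer that mentoring is known to change booking gestation. The documents do not show that. They describe an intended mechanism, and the initial evaluation summarised in the background reports no booking data. Girls who booked before meeting a mentor may be little affected, although community engagement could still act on them. This limits the size of the problem; it does not make the variable baseline.
- **Status of the adjusted model.** A reader might infer that the whole intention-to-treat analysis is compromised. The text does not say whether adjustment applies to the main model, and nothing excludes an unadjusted estimate. The criticism applies to any result that includes this covariate.
- **Only an example.** The covariate follows an e.g., and a full list may sit in an analysis plan. But the protocol names it and calls it baseline, which is a misstatement and not an omission.
- **Never-attenders.** It is tempting to say high-risk girls will be dropped. That assumes complete-case handling, which the protocol does not specify. A no-visit category would keep them but would still adjust for the mediator.
- **A reason to adjust.** Girls are identified after allocation, partly through ANC registers, so the arms could differ in who enters and when. That is a fair motive. This variable, however, cannot separate such selection from the effect of mentoring.

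**Conclusion.** The point stands in a limited form. The protocol labels as baseline a variable that is post-allocation for most girls and lies on its own described pathway. An estimate adjusted for it would not be the intention-to-treat effect.

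Attenuation is the expected direction but not a certainty. It depends on mentoring shifting booking and on booking affecting risk, and unmeasured causes shared by late booking and poor outcome could distort the adjusted estimate further. The range of 0.44 to 0.77 against a target of 0.40 rests wholly on assumed booking shares and odds ratios and should not be read as a forecast. If booking does not differ by arm, nothing is removed. The loss of never-attenders is the smaller part and depends on how missing values are handled.

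This should be fixed but is not critical. The primary outcomes concern feasibility and are untouched; the effect estimate matters mainly for planning the later trial.

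**What to change.** In Proposed analysis, delete gestation at first antenatal visit from the adjustment sentence and report it by arm as an intermediate (process) outcome, with the proportion of girls who never attended ANC alongside it.

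Restrict adjustment to a set named in advance of variables that mentoring cannot change, such as parity, and drop selection on observed imbalance. The minimisation factors (PHU use and distance to referral hospital) may be added. They are cluster-level terms, and the flow chart has only 12 clusters, so few degrees of freedom remain and the set should stay small.

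The cost is one or two sentences. Parity is already named as a covariate, the minimisation factors are needed for allocation, and no new data collection is required.
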